#### Primary hypothesis

The caregivers in the intervention condition show higher levels of sensitive responsiveness post intervention, compared to the childcare providers in the waitlist control group.

#### Secondary hypotheses

The childcare providers in the intervention conditionshow higher levels of mind-mindedness,display higher levels of interactive skills (i.e., respect for child’s autonomy, structuring and limit setting, verbal communication, developmental stimulation, and fostering positive peer interactions), andreport more work-specific resources to cope with stress.Intervention effects on interactive skills are mediated by changes in the caregivers’ mind-mindedness.Intervention effects are moderated by staff stability and the caregiver’s own attachment style:COS-C effects caregivers working in childcare centers characterized by higher levels of staff stability differently than childcare providers working in childcare centers characterized by lower levels of staff stability.COS-C effects caregivers with a secure attachment style differently than caregivers with an insecure attachment style.Intervention effects on interactive skills and mind-mindedness are predicted by childcare provider’s experience of the intervention’s acceptability and feasibility.

## Methods

This protocol paper adheres to the SPIRIT guidelines.

### Trial design

The SECURE (SEnsitive Care: Understanding and REsponding) project is a prospective, parallel, 2-year cluster-randomized controlled trial, where teams of caregivers are randomized to either the COS-C intervention or a waiting-list control group.

### Study setting

SECURE is a collaborative project between the Center for Early Intervention and Family Studies at the University of Copenhagen and the municipality of Høje-Taastrup, in the Capital Region of Denmark. This municipality is a well-suited collaborator as the proportion of at-risk and low-SES families is relatively high compared to other Danish municipalities [63].

### Participants and procedure

Participants are caregivers from early childcare centers for children aged 0–2.9 years from Høje-Taastrup.

In February 2020, all managers of the early childcare centers (*N* = 35) in Høje-Taastrup were invited to participate in the project at a meeting held by the head of public childcare in the municipality and the Principal Investigator (PI, [name]). One of these childcare centers volunteered to participate in the pilot project. The remaining 34 center managers signed up for a visit in their center by the PI where their staff, i.e. the caregivers, were invited to participate. Due to the Covid-19 pandemic, some of these meetings were held online. At these meetings, the caregivers were informed about the project, it was made clear that participation was voluntary, and caregivers in each center were asked to consider whether they were interested in participating in the project. Subsequently, the managers gave their notice of participation to the project team.

While 28 of the initially invited childcare centers signed up for participation, six centers declined to participate. In 2021, two new childcare centers were established in the municipality; they were invited using the same procedure as described above and gave their consent for participation primo 2022. Currently, 30 childcare centers have consented to participate with a team, corresponding to approximately 110 caregivers, and all have been allocated to a time-period (see below for randomization procedures). Should more childcare centers (e.g., centers that are established after project start) be interested in participation, they will be informed about the project and enrolled accordingly. Figure 4 provides an overview of enrollment and allocation in the project. Data collection began in April 2021. Currently, participant enrollment and data collection is ongoing.

**Fig. 4 Fig4:**
[figure not shown]
Flow of participants

Caregivers participate in the COS-C program together with their team. A team of caregivers typically consists of three or four caregivers who have 12–14 children in their care, but some teams are larger. Irrespective of the size of the childcare center, each center participates in the study with one team of caregivers. This is mainly due to budget constrains but it also prevents spill-over effects and contamination within the centers. If more than one team from a childcare center is interested in participation, a random draw will determine which team participates (see randomization procedures below). To be eligible for participation, the participants in the team must be 18 or older, employed on a fixed-term contract, and not be part of the management of the childcare center.

A COS-C group consists of 6–10 participants. To make sure that COS-C groups are neither too small nor too large, teams consisting of four or less participants partake in a COSP-C group with a team from another childcare center whereas teams consisting of five or more caregivers constitute their own COSP-C group.

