**Fig. 3 Fig3:**
[figure not shown]
Ilustration of the development of an avoidant strategy in the child (from Circle of Security International™)

An essential part of the program is the use of pre-produced video vignettes of both problematic caregiver-child interactions and interactions where the caregiver is responsive and sensitive. These are used to illustrate how caregivers’ may or may not struggle in meeting childrens’ emotional needs and to faciliate group reflection and learning.

In addition to the adapted visualization of the Circle of Security (Fig. 2), the COS-C program includes material and exercises on “indentifying the invisible children” (e.g., socially withdrawn children), how to support children and parents during check-in and pick-up situations, how to meet the needs of children who are “hard to connect with”, and naming the children’s feelings [51]. Another important adaption focuses on how to facilitate interactive repair between children which is pivotal for fostering positive peer-interactions.

During the sessions, the COS-C facilitator supports the caregivers in using the Circle of Security graphic to reflect on the video material and on examples from their daily interactions with the children in their care. Moreover, the caregivers are invited to reflect on what may prevent them from meeting a child’s needs in specific situations. This joint reflection is hypothesized to be the mechanism of change for the intervention.

While an important goal of the intervention is to facilitate the caregivers’ reflections on children’s mental states, another is to support the caregivers in reflecting on their own mental states and how these might impact their ability to support the child’s changing needs “on the circle”. In doing so, the COS model fits in the category of mentalization-based interventions, wherein understanding of the child’s behavior and the caregiver’s response is organized through recognizing, appreciating and hypothesizing about mental states of the child, but also those of the caregivers themselves [40].

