### Sample size and power

The primary outcome for the study is the childcare providers’ sensitive responsiveness using the CIP-Scales [52]. Therefore, sample size was determined as the number of participants required to achieve min. 80% power for detecting a change in this measure with a two-sided alpha of 0.05. Two previous RCTs have examined interventions aiming at increasing professional caregivers’ sensitive responsiveness using the CIP-Scales. These studies find medium (*d* = 0.55) to large (*d* = 0.72) effects of the interventions on caregivers’ sensitive responsiveness post intervention. For normally distributed outcomes, a sample of 29 day care centers (15 intervention, 14 control corresponding to 110 caregivers) with each 3.4 caregivers yields a statistical power of 81% to detect an effect size of *d* = 0.55 using a two-sided alpha of 0.05, a correlation between baseline and post-intervention of 0.5 and an ICC of 0.1. This is the conservative estimate using the lowest effect size. If the effect size is 0.72 the statistical power rises to 96%.

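### The stated 81% power treats all 29 centres as independent, although small intervention teams share COS-C groups across centres; allowing for this lowers the figure modestly

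*Protocol article*

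**What the plan says.** **Delivery.** Under Participants and procedure, each centre takes part with one team, typically of three or four caregivers, though some teams are larger. The joining rule is that "teams consisting of four or less participants partake in a COSP-C group with a team from another childcare center"; teams of five or more form a group of their own. The Intervention section sets eight weekly two-hour group sessions. The section on the Circle of Security classroom approach says of the reflection in those sessions: "This joint reflection is hypothesized to be the mechanism of change for the intervention".

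**Comparator.** Under Control condition, waiting-list centres receive no intervention between T0 and T2.

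**Randomization.** Allocation is by centre, 1:1.

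**Power.** Sample size and power assumes "a sample of 29 day care centers (15 intervention, 14 control corresponding to 110 caregivers"), 3.4 caregivers per centre, d = 0.55, a two-sided alpha of 0.05, "a correlation between baseline and post-intervention of 0.5 and an ICC of 0.1". It reports 81% power, against a minimum of 80%, and 96% if d is 0.72. It calls the 0.55 scenario conservative. It mentions no clustering by COS-C group or facilitator.

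**The concern.** Two teams that sit through the same eight sessions with the same facilitator share an influence on their T2 scores that other centres do not share. Where teams are paired, the independent unit in the intervention arm is the COS-C group; in the control arm it is the centre. Randomizing by centre does not remove a dependence that delivery creates afterwards.

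If the power calculation counts paired centres as independent, it understates the variance of the intervention mean. The margin is under one percentage point above the plan's own 80% minimum, so even a small group effect uses it up at the stated sample size. If the primary analysis were built on the same assumption, its standard error would be somewhat too small.

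**Working it through.** **Inputs from the article:** k1 = 15 and k0 = 14 centres, m = 3.4, ICC = 0.1, baseline correlation 0.5, d = 0.55 or 0.72, two-sided alpha 0.05. **Assumed, because the article does not give it:** a group correlation g of 0.05 to 0.10.

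**1. The stated figure.**
- Baseline factor: 1 − 0.5² = 0.75. Centre design effect: 1 + (3.4 − 1) × 0.1 = 1.24.
- Variance = 0.75 × 1.24 × (1/51 + 1/47.6) = 0.03777, so SE = 0.1944.
- d = 0.55: 0.55/0.1944 = 2.830; power = Φ(2.830 − 1.960) = 80.8%.
- d = 0.72: 0.72/0.1944 = 3.705; power = 95.9%.

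These match 81% and 96%. The article's 110 caregivers do not equal 29 × 3.4 = 98.6. Using 110/29 = 3.79 per centre and a t distribution with 27 df also gives 81.0% and 96.0%. Both routes cluster by centre only.

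**2. Adding the group, first form.** Keep the within-centre ICC at 0.1 and let caregivers from the two centres in a group correlate at g, with all intervention centres paired. The intervention design effect becomes 1.24 + 3.4g. The control variance stays at 0.75 × 1.24/47.6 = 0.01954.

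| g | Intervention design effect | Total variance | d/SE | Power, d = 0.55 |
|---|---|---|---|---|
| 0 | 1.24 | 0.03777 | 2.830 | 80.8% |
| 0.02 | 1.308 | 0.03877 | 2.793 | 79.8% |
| 0.05 | 1.41 | 0.04027 | 2.741 | 78.3% |
| 0.10 | 1.58 | 0.04277 | 2.659 | 75.8% |

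**3. Second form.** Add the group variance to the centre ICC. The intervention variance is 0.75 × [0.1/15 + g/G + (1 − 0.1 − g)/51], where G is the number of groups. G = 7.5 means every centre is paired; G = 10 leaves some larger teams on their own.
- G = 7.5: total variance 0.04204 (g = 0.05) and 0.04630 (g = 0.10); power 76.5% and 72.4%.
- G = 10: total variance 0.04079 and 0.04380; power 77.7% and 74.8%.

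**4. Expected enrolment.** The abstract expects 31 centres and 113 caregivers. Take 16 against 15 centres and m = 113/31 = 3.65, so the centre design effect is 1.265.
- First form, all paired: power is 82.7% at g = 0.05 and 80.3% at g = 0.10.
- Second form, 8 groups: the control variance is 0.75 × 1.265/54.7 = 0.01735. The intervention variance is 0.75 × [0.1/16 + g/8 + (0.9 − g)/58.3] = 0.02031 and 0.02435. Power is 80.9% and 76.8%.

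**5. Reference distribution, kept separate.** With 20 df and g = 0, the step 2 calculation already gives 76.8%. That drop from 80.8% comes from using t instead of the normal and has nothing to do with grouping.

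**6. Type I error, if groups were ignored.** Simulating a centre-level t-test with no treatment effect gives two-sided rejection rates of about 5.5%-5.8% at g = 0.05 and 6.3%-6.5% at g = 0.10, with all or nearly all centres paired. With only 5 pairs, the rate at g = 0.10 is about 6%.

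**The case against.** The strongest objections, and what stands of each:

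- **No analysis model is stated.** A reader might infer that the trial will be analysed with a centre effect only and will have an inflated type I error. The article does not support that. A planning ICC does not fix the analysis model, and random effects and degrees of freedom commonly belong in an SAP, which is not shown. The article also does not say that group membership goes unrecorded. This objection stands in full: the type I error figures are conditional.
- **The group correlation is assumed.** A shared mechanism moves the mean; it does not by itself show that groups differ. Manualised sessions and supervised, certified facilitators should limit such differences. At g = 0 the 81% holds. This stands, and it is why only a range is given. In the first form, g = 0.10 is an upper limit: caregivers from different centres would be as alike as colleagues in one team.
- **Not every centre is paired.** Teams of five or more stand alone, so a fall from 15 units to about 8 is the extreme case. This stands; 10 groups gives the smaller losses in step 3.
- **Power of 72%-74% might be quoted as the effect of grouping.** If that comes from the first form with 20 df, much of the drop is the change of reference distribution, and it should not be counted here.
- **Enrolment is expected to exceed 29 centres.** This largely offsets the loss: in the first form, power stays at or above 80% across the assumed range. In the second form it does so only at the lower end.

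None of this changes the fact that the published calculation has no term for a dependence that the delivery rule creates.

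**Conclusion.** The point holds as a modest correction to the power statement. The design is partially nested by the article's own joining rule, and the 81% is reproduced without any group term. For the stated 29 centres and d = 0.55, an assumed group correlation of 0.05 to 0.10 costs about 2.5 to 5 points (78%-76%), or up to about 8 points if group variance is added to the centre ICC and every centre is paired (77%-72%; 78%-75% with 10 groups). The stated power is therefore less conservative than described and probably a little below the 80% minimum at that sample size.

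It does not follow that the trial is underpowered as now expected to enrol, where the normal-approximation figure is about 83%-80% in the milder form. Nor does it follow that the primary test is invalid: a rise to about 5.5%-6.5% would arise only if the model omitted the group. The figures rest on the assumed correlation, on all or most intervention centres being paired, and on reading the ICC of 0.1 as centre-level, which the 3.4 cluster size and the reproduction support.

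**What to change.** - Restate power over a stated range of group correlations, such as 0 to 0.10, using the actual number of COS-C groups and the expected enrolment. Say whether a normal or a t reference is used, so that the two effects are not confused.
- Retain the COS-C group ID for every intervention caregiver.
- In the primary model, include a random effect for COS-C group in the intervention arm alongside the centre effect in both arms, with Satterthwaite or Kenward-Roger degrees of freedom. If an SAP already specifies this, only the power statement needs to change.

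**Cost:** one identifier, a few lines of analysis text, slightly wider intervals and a slightly less favourable stated power. Delivery of the intervention is untouched. The article reports that enrolment and data collection are ongoing, so the change can be made before results are known.

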
### Intervention

The intervention group (50% of the sample, randomly selected) will receive the COS-C intervention between the baseline (T0) and first post-assessment (T2). In this project, the intervention consists of eight weekly two-hour group sessions with 6-8 professional caregivers per group. Througout the intervention, the caregivers are presented to key principles from attachment theory. The first two sessions introduce the model’s framework, i.e. the Circle of Security (Figs. 1, 2) and focus on observational skills and ability to infer children’s attachment and exploratory needs from their behavior. Each following session will then introduce new themes for reflection and learning, such as child emotion regulation and co-regulation and how the caregiver’s own relationship history may influence their caregiving practices, understanding difficult child behavior (“miscues”, Fig. 3) and interactive repair.

The sessions are facilitated by psychologists from the research team who are all trained and certified in the COS-P and COS-C intervention [25, 64]. The psychologists receive ongoing supervision provided by a certified COS-P fidelity coach (the first author).

To support the implementation of COS-C principles, managers of each participating team are invited to participate in the sessions together with their staff. If the managers choose to particpate, they are instructed to participate on equal terms as their staff. Group sessions take place either in the caregivers’ own childcare center or in another avaible location, such as other suited rooms in the municipality. The Municipality ensures that the childcare centers can call in substitutes for the caregivers while they attend COS-C. The COS-C material (i.e. manual handouts and exercises) that is added to the COSP program has been translated into Danish, and is used together with the Danish version of the COSP video-material [65].

### Control condition

Caregivers in the waiting-list control group take part in the T0 and T2 assessments parallel to the intervention group but they do not receive any intervention between asessments, and they are not in any contact with the project team other than for planning and handling practical issues. After T2 data collection, participants in the waiting-list control group attend a COS-C group (T3), followed by a post-intervention assessment with the waiting-list control group only (T4).

### Measures

An overview of the primary and secondary outcome measures is provided in Table 1.

**Table 1 Tab1:** Overview of measures used in the study

	Measure	Time point	Name of instrument	Type
Primary outcome	Caregiver sensitive responsiveness	T0, T2	Caregiver Interactive Profile Scales (CIP-scales [52])	Observation based on video-recordings
Secondary outcomes	Mind-mindedness (representational)	T0, T2	Mind-Mindedness Interview (MM-interview [68])	Interview, coding based on transcript
	Mind-mindedness (interactional)	T0,T2	Mind-Mindedness [67]	Observation, coding based on video-recordings and transcripts of the video
	Caregiver Respect for autonomy, Structure and limit setting, Verbal com-munication, Developmental stimulation, & Fostering positive peer interactions	T0, T2	Caregiver Interactive Profile Scales (CIP-scales [52])	Observation based on video-recordings
	Caregiver resources to cope with work-related stress	T0,T2	The Child Care Worker Job Stress Inventory [69]	Questionnaire
Other measures	Caregiver attachment style	T0	Experiences in Close Relationships – Revised Version (ECR-R [70])	Questionnaire
	Structural factors	T0, T2	Questionnaire designed for the purpose of the study by The Danish Evaluation Institute	Observation and questionnaire
	Acceptability	T0, T2, T4	The Acceptability of Intervention Measure (AIM, [71])	Questionnaire
	Feasibility	T0, T2, T4	The Feasibility of Intervention Measure (FIM, [71])	Questionnaire
	Experiences of the COS-C	T2, T4	The Client Change Interview (CCI) [72]	Interview, semi-structured
	Demographic factors	T0	Developed for the project	Questionnaire

#### Primary outcome measure

*Caregiver Interactive Profiles Scales (CIP-scales*) [52] are used to assess the caregivers’ interactive skills at T0 and T2. This is an observational instrument developed to assess the quality of caregivers’ interactive behavior in center-based childcare with 0–4 year-old children, and has been used to assess the quality of caregiver-child interactions in Western [30, 52] and non-Western childcare settings [66]. Ratings are based on filmed observations of the caregivers in their natural childcare setting where they typically interact with groups of children. To capture a broad range of situations with differing demands, the caregivers in this project are observed in four different situations: diaper change, lunch/snack time, free play, and transition between activities (10 min each). The caregivers are not given any specific instructions and are asked to follow the regular program to capture a usual day.

CIP-scales consists of six scales: (1) Sensitive responsiveness, (2) Respect for autonomy, (3) Structure and limit setting, (4) Verbal communication, (5) Developmental stimulation, and (6) Fostering positive peer interactions. Each interactive skill is rated on a 7-point scale with higher scores indicating higher quality of the skill. Sensitive responsiveness is used as the primary outcome and is the core experimental variable in this study.

The coding manual provides definitions of each interactive skill and describes what characterizes each score. For example, a score in the low (1, 2) range of Sensitive responsiveness is characterized as: “*Hardly provides emotional support to the children. She misses many signals or her reactions are too slow or inadequate. She may show indifferent or detached behavior*” and a score in the high (6, 7) range is described as: “*Shows warm and genuine interest in the children and provides emotional support when needed. In general, the caregiver responds promptly and appropriately to the children’s signals, thereby functioning as a *“*secure base*”* for the children. If unable to respond, she acknowledges having noticed the signal and provides a more complete response as soon as possible*” ([52] p. 778).

The videos will be rated by a trained observer blind to group allocation and with no practical involvement in the intervention and no prior knowledge of the participants. To calculate interrater reliability, 20% of the observations are selected randomly and coded by a second coder blind to group allocation and the primary coder’s ratings. Coders will be trained by the developer of the CIP-scales, [name] (sixth author), and will attend regular meetings to check for adherence to the coding principles and prevent drifting. The coding manual has been translated into Danish by The Danish Evaluation Institute (EVA) in collaboration with the developers of the scale at Netherlands Consortium Kinderopvang Onderzoek.

#### Secondary outcome measures

*Mind-Mindedness* is the second core outcome of the study. MM can be assessed in two ways. “Offline” mentalizing, or representational MM, is assessed by using a well-established, simple interview, addressing the caregivers’ tendency to spontaneously think of the child as a psychological being [67]. “Online” mentalizing, or interactional MM, is assessed by observing the caregiver’s ability to apply a mentalizing stance towards the children during interaction. The interview approach is proposed to assess the representational aspect of MM, i.e. how the caregiver keeps the child in mind in absence, whereas interactional MM is proposed to be a construct at the interface of representational mentalizing and caregiver sensitivity, as it is an interactional construct of “enacted” mentalizing [42]. To capture both interactional and representational MM, two different measures are applied at T0 and T2 for both groups.

*The Mind-Mindedness interview* [68] is used to asses representational MM. We adapted the MM interview to a childcare setting by asking the caregiver to think about two children, whom they perceive as challenging, and are then given an open-ended question: “*Can you describe [child] for me?*”*.* The caregiver is initially informed that there are no right and wrong answers, and that they should talk about the first thing that comes to mind. If they ask for guidelines for answering the question, it is repeated that no specific type of description is required and that they should talk about what comes to mind. After this, a follow-up question is employed: “*Can you say anything else about [child]?*”. The recorded interview is transcribed verbatim, and according to the manual [68] each attribute that refers to the child is classified into one of the following categories: (1) Mental attributes, (2) Behavioral attributes, (3) Physical attributes, (4) General attributes, (5) Self-referential comments and (6) Comments regarding institutional practices. To control for differences in verbosity, representational MM is calculated as the proportion of mental attributes, i.e. number of mental attributes divided by total number of attributes produced by the caregiver.

*Interactional MM* is assessed by observing the caregiver’s use of appropriate mind-related comments during interaction with the children in the childcare center, and thus represents the ability to envision mental states in the children from the children’s behavior and to convey such understanding verbally to the children. Twenty minutes of video-recorded interactions between the caregivers and the children in their care will be used for coding of MM, following the procedure from a previous study [47]. Each video is transcribed verbatim, and then coded following the MM coding manual [67]. First, mind-related comments are identified i.e. if they refer to the child’s thoughts, intentions or feelings. Next, these comments are coded into appropriate or non-attuned comments upon watching the video. Comments are coded as appropriate mind-related comments if (a) the coder agrees with the caregiver’s interpretation of the child’s mental state; (b) the comment links the current activity with similar events in the past or future; (c) the comment refers to the child’s preferences; (d) the comment clarifies how to proceed after a lull in the interaction.

Comments are coded as non-attuned if (a) the coder disagrees with the caregiver’s interpretation of the child’s mental state/s; (b) the caregiver refers to a physical state without overt signs of such; (c) the caregiver refers to a past or future event unrelated to the child’s current activity; (d) the caregiver asks what the children/child want/s, or suggests a new activity when the child is already engaged with something else; (e) the caregiver seems to be attributing internal states that were not implied by the child’s behavior and thus appeared to be projections of the caregiver’s own internal state; and (f) the referent of the comment is not clear. We will code for caregiver mind-mindedness in a group of children, i.e. differentiating between dyadic and non-dyadic mind-mindedness, following Colonnesi and colleagues’ adaptation to the original mind-mindedness coding scheme [48].

*CIP scales* [52] (described above) other than Sensitive responsiveness. i.e., Respect for autonomy, Structure and limit setting, Verbal communication, Developmental stimulation, and Fostering positive peer interactions are used for assessing caregiver interactive skills, as secondary outcomes. All interactive skills are measured with the CIP scales in both groups at T0 and T2. *The Child Care Worker Job Stress Inventory* [69] is used to test the effect of the COS-C on the caregivers’ work-specific resources to cope with stress (e.g. feeling they are helping children develop, feeling close with children, feeling their work is valued). The instrument has demonstrated high validity and internal consistency and is developed specifically for childcare workers in both center- and home-based settings. It consists of three scales out of which we use the Job Resources Scale. This scale consists of 17 questions that are rated on a 5-point Likert scale from Rarely/never (= 1) to Most of the time (= 5). Higher scores reflect more access to resources to manage job-related stress. The questionnaire has been translated and adapted to the Danish context by the first and last author for the purpose of this study, and face validity of the questions was tested on a pilot group of eight caregivers. The measure is part of a online survey that is distributed to participants in both groups at T0 and T2.

